| 1. **Objectives, Specific Aims and Rationale**   *Objective*  To investigate the use of antibiotics and their protective effect against complications of infection to inform the development of risk prediction models to guide antibiotic treatment decisions for suspected infection in primary care.  *Aims*   1. Estimate the incidence of i) GP consultations for infection and ii) antibiotic prescriptions by: age-group, gender, SES, ethnicity, selected co-morbidities, obesity and smoking status 2. Describe antibiotic prescribing patterns linked to the reason for the prescription by: age-group, gender, SES, ethnicity, selected co-morbidities, obesity and smoking status 3. Estimate the incidence of adverse outcomes in the following 28 days including: hospital admission for infection; A&E admission; re-consultation for infection; re-consultation for antibiotic side-effects (rash, nausea, …) and death for patients with a GP consultation for i) respiratory tract infection ii) urinary tract iii) skin/soft tissue infection, comparing patients with each listed age/co-morbidity group (including smoking status and obesity) to non-comorbid patients 4. Estimate the number of patients needed to treat with antibiotics to avoid one infection-related adverse outcome, comparing the results for each age/co-morbidity group to non-comorbid patients 5. Develop risk prediction tools to support clinical decision making and communication with patients   *Rational*  We have previously shown that more than half of all antibiotic prescriptions in primary care are issued to less than 10% of patients, and that this 10% of patients have high levels of co-morbidity.1 Targeting such high-frequency users of antibiotics in antimicrobial stewardship programmes might provide opportunities for a more effective intervention approach. Underlying this hypothesis is the assumption that it might be safe and feasible to reduce prescribing in patients with the highest levels of antibiotic prescribing, many of whom have co-morbidity.  To investigate whether higher rates of antibiotic use are likely to be justified in higher risk patients compared to patients who lack these risk factors, we will undertake a series of studies to investigate which patients in terms of age, gender, SES, ethnicity, selected co-morbidities, obesity and smoking get the most antibiotics. We will determine which patients are most likely to receive antibiotics for which infections and relate this to national guidance on antibiotic prescribing. To estimate whether the protective effect of antibiotics differs according to the patient’s age and the presence of co-morbidity, obesity or their smoking status, we will estimate the risk of infection related adverse-outcomes, comparing patients who have been treated with antibiotics to those who have not been treated with antibiotics for each of these groups. We will use these estimates to calculate the number of patients who need to be treated with antibiotics to avoid one infection-related adverse outcome (NNT), accounting for age, gender, SES, ethnicity, co-morbidity, obesity and smoking status. This will inform the development and validation of individualised risk-prediction models to support clinical decision-making and patient communication around the need for antibiotic treatment for suspected infection in primary care. |

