| 1. **Study Design**   For this study, we will use a retrospective cohort study design, looking at patients with consultations for infection and/or antibiotic prescribing between 1st April 2007 and 31st December 2015. (for an exact definition see *K. Study population* and *Error: Reference source not found*)  In a first step (Objective 1), we will describe the incidence of GP consultations for infection and the incidence of antibiotic prescribing in the main study population. This will provide important context on the burden of infection and frequency of antibiotic use in primary care.  Within the main study population, we will then undertake a nested cross-sectional study looking at all antibiotic prescriptions in the main study population. For each prescription we will use Read codes on the day of the prescription to establish the reason for the prescription. (Objective 2) This will inform our understanding of why antibiotics are prescribed.  Next, we will undertake a series of cohort studies focused on specific infectious syndromes within the main population. Three nested cohorts will be built based on a GP consultation for a) respiratory tract infection, b) urinary tract infection and c) skin/soft tissue infection. For each cohort, we will estimate the rate of infection-related adverse outcomes within 28 days of the initial GP consultation for patients with and without antibiotic treatment. (Objective 3)  In order to determine the protective effects of antibiotics against these adverse outcomes, we will then estimate the Number Needed To Treat with antibiotics (NNT) to prevent one additional adverse outcome. In particular, we will compare the NNT for patients with and without co-morbidities of interest, obesity or smoking. (Objective 4).  Finally, we will synthesize out analyses in objectives 1-4 to develop a risk model for each cohort (respiratory, urinary and skin/soft tissue models). These models will support clinical decisions and patient communication around the need for antibiotic treatment for suspected infection (Objective 5).  Results across all steps will be stratified or adjusted by age, gender, SES, ethnicity, co-morbidity, obesity and smoking status. |

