| 1. **Study population**   The study period will be from 1st April 2007 to 31st December 2015.  We will perform all analyses in patients that were eligible for all linkages and fulfil the following:   1. registered at a participating English practice prior to the transfer of identifiers to the trusted third party for matching for at least a year before their entry into the study 2. their practice is deemed to be contributing ‘up-to-standard' (UTS) data at study start date 3. they had a valid identifier for linkage (NHS number for ONS mortality and HES data, postcode for IMD) 4. they had not opted out or dissented from CPRD or the linkage scheme 5. individual record is of ‘acceptable' research quality as verified by the CPRD.   **Cohort 1**: Individuals who were registered with a GP contributing to CPRD between 1st April 2007 and 31st December 2015 and who have a complete record on age, gender and IMD are eligible for inclusion in this study (see *P. Plans for addressing missing data*). Patients must have been registered with their GP for at least one year before entering the study with the exception of children aged less than one year who will be assumed to be born into the Practice. Patients can enter the study late or leave the study early in order to include patients who died within the study period (who might be inherently less healthy). Patients enter the study population on the latest of the following dates: continuous registration with GP for 12 months or 1st April 2007. Where patients registered with their GP after the 1st April 2007, patients enter the cohort after 12 months of continuous registration. Patients exit the cohort on the earliest of the following dates: the date the patient died, the date the patient left the practice, or 31st December 2015.  Subsequent studies are nested within cohort 1 (see Error: Reference source not found):   1. Nested cross-sectional study: Patients within cohort 1 with at least one prescription of an antibiotic 2. Nested cohort studies of specific infection syndromes: Patients within cohort 1 with at least one GP consultation for a specific infection syndrome (respiratory, urinary, skin/soft tissue). For these cohorts, patients will enter the cohort on the day of the consultation for infection. Patients will leave the cohort on the earlier of: 28 days after initial consultation, death, transfer out of practice or 31st December 2015. Patients can enter and exit the cohort more than once. |

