| 1. **Data/ Statistical Analysis**   *1. Estimate the incidence of i) GP consultations for infection and ii) antibiotic prescriptions*  For every patient in cohort 1, data on all consultations for infection and antibiotic prescriptions occurring within the study period will be extracted. We will estimate the incidence of GP consultations for infection and antibiotic prescriptions. This will be done for all consultations and prescriptions, and then separately for each category of infection and each class of antibiotics, based on chapter 5.1 of the British National Formulary (BNF) (see Appendix Tables 1 & 2). The denominator will be estimated as total person-time contributed by patients in the cohort during the study period. We will use Poisson regression to estimate the adjusted rate of consultation and prescription, taking account of the effect of age, gender, SES, ethnicity, selected co-morbidity, smoking and obesity. Random effects will be included to take account of clustering of observations by practice. Rates will be assessed for overdispersion by additionally fitting a negative binomial model and testing for alpha greater than zero via a likelihood-ratio test. If rates are found to be overdispersed, the negative binomial model will be used instead of a Poisson model. Adjusted rate ratios will be presented with 95%-confidence intervals.  *2. Describe antibiotic prescribing patterns linked to the reason for prescription*  The overall number of antibiotic prescribing episodes will be calculated for each patient individually, counting all recorded prescriptions between 1st April 2007 and 31st December 2015. For each episode, a clinical indication will be ascertained. Read codes for a diagnosis or symptom of infection recorded on the same day as the antibiotic prescription will be assumed to represent an indication for the prescription. Where more than one possible indication within the same type of infection is recorded on the day of prescription, the more granular code will be used. If multiple indications across different types of infection are recorded, the prescription will be labelled as having multiple indications. Conversely, if no infectious indication for a prescription was found, the prescription will be labelled as having no infectious indication and we will look for any non-infectious codes associated with the date of antibiotic prescription. The ten most common indications will be established and compared to the same numbers for the period from 1998-2001.14 This approach will be replicated for each class of antibiotics based on chapter 5.1 of the BNF. Patterns of repeat consultation or prescription during episodes of infection which may be prolonged will be investigated for each antibiotic prescription extracted in objective 1. We will define a new episode as a consultation or prescription recorded at least 28 days after any previous consultation for infection or antibiotic prescription. We will undertake sensitivity analyses to investigate the impact of using different time periods to define an episode. We will also examine the use of regular (prophylactic) antibiotic treatment.  Proportions and appropriate 95%-confidence intervals will be calculated and all results will be stratified by age-group, gender, SES, ethnicity, selected co-morbidity, obesity and smoking status. Descriptive data will be displayed graphically.  *3. Estimate the incidence of adverse outcomes in the following 28 days*  For each of the selected clinical infection syndromes in the nested cohort study, events in CPRD, HES and ONS will be searched for all adverse outcomes of interest (see *M.* Exposures, Health Outcomes§ and Covariates). Crude incidence rates of for each outcome will be calculated for patients who were treated (exposed) and not treated (unexposed) with an antibiotic. The denominator will be estimated as the total person-time contributed by patients at risk of each adverse outcome, taking account of the fact that this will be different for each outcome. For example, exposed and unexposed patients cannot consult General Practice if they have been admitted to hospital and should therefore not contribute to the denominator during this period when estimating rates of GP re-consultation in the 28 days following consultation for infection. A Poisson regression model will be used to estimate adjusted rates of adverse outcomes in each group, controlling for age, gender, socio-economic status, ethnicity, co-morbidity, obesity and smoking status and assessing for interaction between age and co-morbidity. Random effects will be included to take account of clustering of observations by practice. If the outcomes are overdispersed, negative binomial models will be used instead of Poisson models. Adjusted rate ratios will be presented with 95%-confidence intervals.  *4. Estimate the number of patients needed to treat with antibiotics to avoid one infection-related adverse outcome*  For each clinical infection syndrome-related adverse outcome identified in objective 3, the odds of that outcome in the 28 days following consultation for those treated with antibiotics (unexposed) and not treated with antibiotics (exposed) will be estimated using logistic regression. We will calculate adjusted odds ratios for the protective effect of antibiotics, adjusting for age, gender, SES, ethnicity, year/season, co-morbidity and the probability of receiving antibiotic treatment (see *O. Plan for addressing confounding*) and assessing for interactions with age and co-morbidity. We will use mixed models to adjust for clustering at a practice level and to take account of clustering of observations within a patient due to repeat episodes of infection. Where there is a significant effect of antibiotics between treated and untreated patients, the NNT or NNH to prevent one individual from developing an adverse outcome is calculated as *1/(absolute risk difference)*. A significant effect will be defined by a p-value < 0.05 for the coefficients of antibiotic treatment and its interactions. To avoid an arbitrary cut-off point, p-values close to 0.05 will also be assessed but discussed separately. The NNT will then be used to assess the clinical relevance of any significant differences found. Whilst the relative risk reduction (RRR) may be similar, the NNT may be different due to differing background risk. This will be explored.  *5. Develop risk prediction tools to support clinical decision making*  For each cohort (i.e. for each of the clinical syndromes of UTI, RTI and SSTI), we will develop a logistic regression risk model to predict the risk of adverse outcomes if patients are treated versus not treated with antibiotics. Models will be developed on a random sample of 80% of the observations within a cohort, reserving 20% of the data to estimate the model’s predictive performance.  A negative outcome will be defined as the occurrence of any of the following within 28 days following the index consultation: hospital admission for infection or complication; re-consultation for infection; A&E admission; death. Antibiotic treatment will be defined as a prescription of an antibiotic on the day of consultation for clinical syndrome. Risk factors will be selected based on the analyses outlined in objectives 1-4 and broadly grouped into: socio-demographic variables, co-morbidity and clinical presentation. Biologically plausible interactions between risk factors and age and between risk factors and co-morbidities will be examined.  Whereas age and sex will be forced into the model, other risk factors will be added in order of their significance in objective 4. Risk factors will be kept in the model if they improve the predictive performance of the model as defined by model discrimination and model calibration.17 For example, a risk factor will be used in the model if it improves discrimination and/or calibration. If a variable improves discrimination but reduces calibration, it will still be included in the model, but will be omitted if it increases calibration at the cost of discrimination.  Model discrimination, i.e. the model’s ability to correctly identify patients with and without an outcome, will be estimated using the concordance (c) statistic.18 The c statistic represents the probability that between two randomly chosen patients, one with the outcome and one without, the model assigns a higher score to the patient with the outcome. As a second measure, model calibration will be assessed using the Hosmer-Lemeshow test.18 We will additionally assess model calibration graphically for reasons for poor calibration by comparing the mean observed outcome in deciles of predicted risk. In this calibration plot, the intercept indicates the extent to which predictions are systematically too low or too high, while the slope reflects overfitting of the model.  For each model, we will estimate the internal validity of discrimination and calibration estimates using cross-validation with bootstrap subsampling based on 1000 iterations. In a secondary analysis, we will assess model performance in subgroups by age, sex and co-morbidity.  Finally, we will develop a simplified scoring system using the risk factors in the model,17 assigning the total score to a specific absolute risk of adverse outcomes in the 28 days following consultation, comparing outcomes if an individual is treated versus not treated with antibiotics. We will assess the predictive performance of the risk scores using the approaches outlined above. |

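### The protocol promises to show which patients are most likely to receive antibiotics for which infections, but no analysis in section N estimates that likelihood

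*Protocol*

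**What the plan says.** The rationale under Objectives, Specific Aims and Rationale states: "We will determine which patients are most likely to receive antibiotics for which infections and relate this to national guidance on antibiotic prescribing". The Technical Summary, Study Type and Selection of comparison group(s) or controls sections express a matching general intent: to describe the antibiotic treatment of patients with infection syndromes, to relate prescribing to consultation, and to compare prescribing rates across subgroups.

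Aim 2, the aim closest to that promise, is worded as: "Describe antibiotic prescribing patterns linked to the reason for the prescription by: age-group, gender, SES, ethnicity, selected co-morbidities, obesity and smoking status". Study Design makes it a "nested cross-sectional study looking at all antibiotic prescriptions in the main study population", and section K fixes its population: "Nested cross-sectional study: Patients within cohort 1 with at least one prescription of an antibiotic". In section N, step 2, the link runs from the prescription back to a code: "Read codes for a diagnosis or symptom of infection recorded on the same day as the antibiotic prescription will be assumed to represent an indication". The output is: "Proportions and appropriate 95%-confidence intervals will be calculated and all results will be stratified by age-group, gender, SES, ethnicity, selected co-morbidity, obesity and smoking status".

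Step 1 of section N covers consultations and prescriptions: "This will be done for all consultations and prescriptions, and then separately for each category of infection and each class of antibiotics". Its denominator is person-time: "The denominator will be estimated as total person-time contributed by patients in the cohort during the study period".

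**The concern.** Guidance on whether to prescribe applies at the consultation: a patient presents with an infection and is or is not given an antibiotic. The matching quantity is the probability of a prescription given a consultation for infection X in group G. Step 2 conditions the other way and gives the probability that a prescription was for infection X, given that one was issued in group G. Consultations that ended without an antibiotic are outside its denominator.

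The distinction bears on the study's own question. The rationale asks whether higher antibiotic use in higher-risk patients is justified. The background contrasts COPD, where more prescribing might be warranted, with obesity, where the indication is less clear. A group may receive many antibiotics for an infection because it consults more often, or because it is prescribed to more readily once it consults. These call for different stewardship action, and shares of prescriptions do not separate them.

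**Working it through.** The protocol states no figure for this objective, so there is none to reproduce. The check has two parts.

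**1. What each planned analysis conditions on**

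- Step 1: consultations and prescriptions, each over person-time. Even if read as giving prescription rates by infection category, a rate per person-time is the product of how often a group consults and how often it is treated when it does. No ratio of the two rates is specified.
- Step 2: issued prescriptions only; shares by indication.
- Steps 3 and 4: syndrome cohorts entered at a consultation, treated and untreated; the results are rates and odds of adverse outcomes, and the number needed to treat.
- Step 5: the same cohorts; the result is predicted risk of an adverse outcome.
- Propensity score (section O): models the probability of treatment, but only to adjust for confounding. Reporting it by infection and patient group is not planned.

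None reports the proportion of consultations for an infection that led to an antibiotic, by patient group.

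**2. Whether step 2 shares can stand in for that proportion**

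All inputs here are assumptions chosen for illustration. Consultations are per 1,000 person-years, in the order respiratory / urinary / skin. Prescriptions = consultations × probability of an antibiotic per consultation. Share = prescriptions for that infection ÷ all prescriptions in the group.

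| Group | Consultations | Probability per consultation | Prescriptions | Total | Shares |
|---|---|---|---|---|---|
| A | 200 / 40 / 80 | 0.60 / 0.90 / 0.60 | 120 / 36 / 48 | 204 | 58.8% / 17.6% / 23.5% |
| B | 400 / 80 / 160 | 0.30 / 0.45 / 0.30 | 120 / 36 / 48 | 204 | 58.8% / 17.6% / 23.5% |
| C | 500 / 40 / 60 | 0.40 / 0.90 / 0.60 | 200 / 36 / 36 | 272 | 73.5% / 13.2% / 13.2% |
| D | 150 / 60 / 100 | 0.70 / 0.90 / 0.60 | 105 / 54 / 60 | 219 | 47.9% / 24.7% / 27.4% |

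A against B: the shares are identical, and so are the prescription rates (204 per 1,000 person-years), yet A is twice as likely to be treated at each consultation (0.60/0.30 = 2; 0.90/0.45 = 2). Only the consultation rates differ (320 against 640 in total).

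C against D: C has the larger respiratory share (200/272 = 73.5% against 105/219 = 47.9%) but the smaller chance of an antibiotic per respiratory consultation (0.40 against 0.70). The ranking reverses.

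**The case against.** The strongest reply is that the intent is stated elsewhere and the rest is detail for a statistical analysis plan. The Technical Summary speaks of describing the antibiotic treatment of patients with common infection syndromes by patient characteristics. Study Type promises relationships between prescribing and consultation. The comparison-group section covers prescribing rates in the cohort studies as well as the cross-sectional one. The syndrome cohorts hold treated and untreated consultations, so the proportion treated could be read off for three broad syndromes. Step 1 consultation rates by infection category would also expose a large difference in consulting such as that between A and B. Finally, the sentence in the rationale names no objective, and Aim 2 as worded is met by a prescription-based design.

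Much of this stands. A reader might infer that the study lacks the data, that it never relates prescribing to consultation, or that it cannot answer the question. The documents do not support any of these: cohort 1 holds the consultations, and the general intent is written down. Nor is step 2 useless against guidance: indication by drug class, and prescriptions with no infectious indication, can be set beside guidance without a consultation denominator.

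What does not stand is that only detail is missing. Section N sets out the analysis for each objective, and for the one nearest the promise it fixes a population that leaves out untreated consultations. Dividing one step 1 rate by another is not specified. It would also require prescriptions to be classified by infection category, which the wording of step 1 leaves open.

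**Conclusion.** The point holds as a mismatch between a stated purpose and the stated analyses. Followed exactly, section N would not deliver the likelihood of receiving an antibiotic for a given infection by patient group. A comparison with guidance drawn from step 2 shares would mix consulting more with being prescribed to more readily.

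The actual size is unknown. The two-fold difference and the reversed ranking come from assumed inputs; they show that shares do not determine the probability per consultation, not how far the two diverge in these data. The conclusion also rests on reading the promise as a probability per consultation. That is the natural sense beside prescribing guidance, but it is not spelt out. The number-needed-to-treat and prediction objectives are unaffected. The change should be made, but it is not critical to the study.

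**What to change.** In step 2 of section N, add the coded infection consultations already extracted in step 1 as a denominator. Report the proportion with an antibiotic prescribed on the day of consultation, which is the definition of treatment already used in step 5, by infection type and by each listed patient group. Give adjusted estimates from a logistic model with practice and patient effects, in line with the clustering already planned for step 4. Base the statement on who is most likely to receive antibiotics, and the related guidance comparison, on these proportions. Keep the shares of prescriptions by indication and drug class as description.

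The cost is one further table and model, with no new data. The proportions would cover coded consultations only, and the limitations section already acknowledges that coding is incomplete and varies between practices. The Amendments section reports that steps 1 and 2 have already been run, so the addition should be recorded as a dated amendment.

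If the analysis is not wanted, the minimum is to reword the rationale so that it promises only the distribution of indications among issued prescriptions.

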| 1. **Exposures, Health Outcomes§ and Covariates**   **§***Please note:**Summary information on health outcomes (as included on the ISAC application form above) will be published on CPRD’s website as part of its transparency policy*  *Exposure*  Exposures will include i) prescription of an antibiotic ii) GP consultation for suspected infection (see Appendices: Table 1 – Codelist for antibiotics, Table 2 – Codelist categorising indications for antibiotic use and Table 3 – Codelists to identify patients with suspected respiratory tract, urinary tract or skin/soft tissue infection)  *Health Outcomes*  The following outcomes (within 28 days of presentation in primary care) will be separately considered for analysis:   - Re-consultation for the same type of infection (CPRD; see Appendix Table 3) - Re-consultation for a side effect of antibiotic treatment (CPRD; see Appendix Table 4a –side effects of antibiotic treatment) - Complications of infection in primary or secondary care (CPRD and inpatient HES; see Appendices: Table 4b and 4c – complications of infection; depending on the indication) - Admission to Accident & Emergency (HES A&E) - All-cause hospitalisation (inpatient HES) - All-cause mortality (CPRD, HES and ONS)   We will undertake a sensitivity analysis to investigate the impact of excluding outcomes that occur on the same day as the exposure. The impact of different time windows will be explored, informed by a literature review on the natural history of the duration of different infections.  *Covariates*  We will include the following covariates:   - Age (classified as 0-4, 5-17, 18-44, 45-64, 65-84, 85-94 and 95+, years of age inclusive) - Sex (female and male) - Index of Multiple Deprivation (IMD; 1-5) - Co-morbidities (coded as indicator variables based on national guidance from Public Health England3 and feasibility1; see Appendix Table 5 for comorbidity code list)   - Diabetes   - Chronic Kidney Disease (CKD)   - Chronic Obstructive Pulmonary Disease (COPD)   - Asthma - Obesity - Smoking status15 - Season (months or quarters) and year - Ethnicity   We will undertake a sensitivity analysis of the impact of coding co-morbidities as binary indicator variable and as total number of co-morbidities. |

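### Nested-cohort index consultations have no look-back, so some recently treated patients can enter the treated/untreated comparison as new, untreated cases

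*Protocol*

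**What the plan says.** Protocol section K (Study population) defines entry to the three nested syndrome cohorts: "patients will enter the cohort on the day of the consultation for infection". On exit it says: "Patients will leave the cohort on the earlier of: 28 days after initial consultation, death, transfer out of practice or 31st December 2015". It adds: "Patients can enter and exit the cohort more than once". No period free of infection consultations or antibiotics is required before an index consultation.

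Section N (Data/Statistical Analysis), Objective 2, gives the only definition of a new episode: a consultation or prescription "recorded at least 28 days after any previous consultation for infection or antibiotic prescription". The same paragraph says: "We will also examine the use of regular (prophylactic) antibiotic treatment". Neither section K nor Objectives 3 to 5 refer back to this rule.

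Treatment is defined once, under Objective 5: "Antibiotic treatment will be defined as a prescription of an antibiotic on the day of consultation for clinical syndrome". Objectives 3 and 4, which produce the rate ratios, odds ratios and NNT, compare treated with untreated patients but give no exposure window. Section M lists re-consultation for the same type of infection within 28 days as an outcome.

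**The concern.** The treated/untreated contrast, and how it varies with co-morbidity, are the main effects named in section I (Sample size considerations). Both depend on the untreated group being untreated. Without a look-back, a patient part-way through a course, or on long-term prophylaxis, can be indexed as a fresh case and labelled untreated because nothing was issued that day. Other index consultations are late returns in an illness that has not resolved, with a different risk from a first presentation.

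The problem need not be even across subgroups. Section D (Objectives, Specific Aims and Rationale) reports that more than half of prescriptions go to less than 10% of patients, who have high co-morbidity. Recent antibiotic exposure is therefore plausibly more common in the groups whose NNT is to be compared with that of non-co-morbid patients.

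**Working it through.** **1. What the two rules admit.** R is a respiratory consultation and Rx an antibiotic. The section K rule is read together with its exit at day 28.

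| Timeline | Respiratory index under section K | Under the Objective 2 rule |
|---|---|---|
| R day 0 with Rx; R day 7 without | day 0 | day 0 |
| R day 0 with Rx; R day 20 with Rx; R day 30 without | days 0 and 30 | day 0 |
| Urinary infection with Rx day 0; R day 5 without | day 5 | none |
| Rx without an infection code day 0; R day 4 without | day 4 | none |

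The first row is the ordinary early return visit, and the rules agree on it. In the other three, section K adds an index 10, 5 and 4 days after a prescription. Under a same-day exposure rule each is untreated. A prescription shortly before entry to cohort 1 has the same effect.

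**2. Anchoring the inputs.** Section I gives OR 0.69, outcome risk 2.4%, 5% significance and 80% power. Taking 2.4% as the untreated risk p0:

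- untreated odds = 0.024/0.976 = 0.02459
- treated odds = 0.69 × 0.02459 = 0.01697, so p1 = 0.01668
- NNT = 1/(0.02400 − 0.01668) = 137

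The Wald formula N = (1.960 + 0.842)² × [1/(x·p1(1−p1)) + 1/((1−x)·p0(1−p0))] / (ln 0.69)² needs the treated share x, which the protocol text does not give. Solving for it gives x = 0.80, and N is then 16,511 (stated 16,512). At 0.04% risk it is 971,057 (stated 971,057). This supports reading 2.4% as the untreated risk.

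**3. Scenario A: part of the untreated group is already covered.** Let a share f (assumed) of untreated indexes carry the treated risk: q = (1−f)·p0 + f·p1. Observed OR = [p1/(1−p1)]/[q/(1−q)] and NNT = 1/(q−p1).

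| f | OR | NNT |
|---|---|---|
| 0 | 0.69 | 137 |
| 5% | 0.701 | 144 |
| 10% | 0.712 | 152 |
| 20% | 0.736 | 171 |
| 30% | 0.761 | 195 |

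If f were 5% in non-co-morbid and 20% in co-morbid patients (assumed), a false interaction of 0.736/0.701 = 1.05 would appear.

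**4. Scenario B: part of the untreated group is a continuing, worse episode.** Let a share g (assumed) have k times the untreated risk: q = (1−g)·p0 + g·k·p0.

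| g | k | OR | NNT |
|---|---|---|---|
| 5% | 1.5 | 0.673 | 126 |
| 10% | 2 | 0.626 | 103 |
| 20% | 3 | 0.488 | 59 |

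**5. Where the sign changes.** If the misclassified patients have exactly the untreated risk, that is 0.0240/0.01668 = 1.44 times the treated risk, there is no bias. Below that the OR moves towards 1; above it, away from 1.

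**The case against.** Several points on the other side stand.

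- A reader might infer that every infection consultation becomes a new index. The text does not support that: the patient stays in the cohort until day 28, re-entry follows exit, and a same-type return within 28 days is an outcome.
- A reader might infer that attenuation and an inflated NNT are certain. Steps 3 to 5 show that the direction depends on the risk the misclassified patients carry, which the protocol does not give.
- The same-day treatment definition is stated only for Objective 5, which section L describes as prediction without comparison. Carrying it into Objectives 3 and 4 is an assumption, although no other definition is offered.
- Objective 4 speaks of repeat episodes of infection, so the authors may have meant the Objective 2 rule to apply throughout. Section K does not say so, and its entry and exit rules, followed literally, give a different cohort.
- Frequent antibiotic users are the study's target. A strict look-back removes them preferentially.

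The argument that existing provisions already deal with this does not stand. The mixed model handles correlation within patients, not exposure misclassification. The propensity covariates are open-ended, but the examples in section O are prior hospitalisation and immunosuppression; recent antibiotic use is not named. The time-window analysis in section M is stated for outcomes, and the varied episode length in section N belongs to Objective 2. Neither is said to change nested-cohort entry.

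**Conclusion.** The concern holds in a limited form. Section K fixes cohort entry without a look-back, and the protocol's own episode definition would give a different cohort. The affected indexes are chains running past day 28, recent antibiotics for another syndrome or without an infection code, prophylaxis users, and events just before cohort 1 entry. The misclassification of exposure follows if treatment means a same-day prescription.

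Its size is not known from the protocol. Over the assumed ranges, the OR of 0.69 could appear anywhere from 0.76 to 0.49 and the NNT of 137 anywhere from 195 to 59. Scenario A also assumes that a course given for another infection protects fully against the index infection's outcomes. The illustrative false interaction of 1.05 is small against the detectable value of 0.83 in section I (1/0.83 = 1.20). For the main effect, section I claims power to detect an OR of 0.975 (1/0.975 = 1.026), and a shift from 0.69 to 0.712 is already a factor of 1.03. A larger sample will not remove such a bias. This should be corrected before the comparison is run; it does not invalidate the design.

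**What to change.** In section K, apply the Objective 2 new-episode rule to index consultations used for the treated/untreated comparison in Objectives 3 to 5: no infection consultation and no antibiotic prescription in the previous 28 days, looking back before cohort entry. The 12 months of prior registration already supply the data; for children under one, the look-back runs from birth.

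State one exposure definition for Objectives 3, 4 and 5. Analyse patients on regular prophylactic antibiotics as a separate group, since a prescription covering more than 28 days would pass the look-back. Report the unrestricted cohort, adjusted for recent antibiotic use, as a sensitivity analysis so that frequent users remain represented.

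The cost is a few sentences and some lost index consultations, more of them among frequent and co-morbid users, which narrows the population behind the main estimate. The share lost is not given. An assumed loss of 5-30% leaves 637,516 to 469,749 in the urinary cohort, the smallest (671,070 × 0.95 and × 0.70), against the stated 258,247. That requirement is for an interaction and depends on co-morbidity prevalence, so interaction power should be rechecked with the co-morbidity share that remains.
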